## Abstract

**Background**: COVID-19 is a respiratory disease caused by a novel coronavirus (SARS-CoV-2) and causes substantial morbidity and mortality. There is currently no vaccine to prevent COVID-19 or therapeutic agent to treat COVID-19. This clinical trial is designed to evaluate chloroquine as a potential therapeutic for the treatment of hospitalised people with COVID-19. We hypothesise that chloroquine slows viral replication in patients with COVID-19, attenuating the infection, and resulting in more rapid decline of viral load in throat/nose swabs. This viral attenuation should be associated with improved patient outcomes.

**Method**: The study will start with a 10-patient prospective observational pilot study following the same entry and exclusion criteria as for the randomized trial and undergoing the same procedures. The main study is an open label, randomised, controlled trial with two parallel arms of standard of care (control arm) versus standard of care with 10 days of chloroquine (intervention arm) with a loading dose over the first 24 hours, followed by 300mg base orally once daily for nine days. The study will recruit patients in three sites in Ho Chi Minh City, Vietnam: the Hospital for Tropical Diseases, the Cu Chi Field Hospital, and the Can Gio COVID hospital. The primary endpoint is the time to viral clearance from throat/nose swab, defined as the time following randomization until the midpoint between the last positive and the first of the negative throat/nose swabs. Viral presence will be determined using RT-PCR to detect SARS-CoV-2 RNA.

**Discussion:** The results of the study will add to the evidence-based guidelines for management of COVID-19. Given the enormous experience of its use in malaria chemoprophylaxis, excellent safety and tolerability profile, and its very low cost, if proved effective then chloroquine would be a readily deployable and affordable treatment for patients with COVID-19.

**Trial registration:** Clinicaltrials.gov
NCT04328493 31/03/2020

## Introduction

### Background

Coronaviruses (CoVs) are positive-sense single stranded enveloped ribonucleic acid (RNA) viruses, many of which are commonly found in humans and cause mild symptoms. Over the past two decades, emerging pathogenic CoVs capable of causing life-threatening disease in animals and humans have been identified, namely swine acute diarrhoea syndrome coronavirus (SADS-CoV), severe acute respiratory syndrome coronavirus (SARS-CoV), and Middle Eastern respiratory syndrome coronavirus (MERS-CoV) and
1–
3.

In December 2019 the Wuhan Municipal Health Committee identified an outbreak of viral pneumonia cases of unknown cause. Coronavirus RNA was quickly identified in some of these patients
^4^. This novel coronavirus has subsequently been named as SARS-COV-2 and has 89% nucleotide identity with bat SARS-like-CoVZXC21 and 82% with that of human SARS-CoV
^5^. The disease caused by this virus has been designated coronavirus disease 2019 (COVID-19). SARS-CoV-2 has spread rapidly following its initial identification in Wuhan, Hubei Province, China
^6^. On January 5, 2020 there were 59 confirmed cases. As of 5th May 2020, the SARS-CoV-2 pandemic has resulted in more than 3,660,055 confirmed infections globally, with disease reported in over 210 countries, and more than 252,675 deaths. The crude global mortality is currently around 3.4%, significantly greater than that reported for seasonal influenza, which affects up to 1 billion people each year and causes between 290,000 and 650,000 deaths
^7^. Disease is reported from the majority of countries in the Asia-Pacific region, with large numbers affected in South Korea (<8000), and disease also confirmed in Vietnam, Thailand, Singapore, Malaysia, Philippines and Indonesia. Outside the Asia-Pacific region, exponential growth in the number of cases is seen in most European countries, notably Italy, Spain, Germany, France, Switzerland and the United Kingdom. Similar patterns of spread are seen in the Americas, with the USA now reporting more than 1,212,955 cases
^7^.

The main route of spread of COVID-19 is believed to be through respiratory droplets; however, other routes including the faeco-oral transmission route and fomites may be important
^6^. Currently there is no proven effective prophylaxis, treatment or vaccine. The estimated COVID-19 basic reproductive ratio (R0) of 1.25 to 3.0 is similar to or higher than that of seasonal (1.3) or pandemic influenza (1.4 to 1.8)
^8,
9^. The use of personal protective equipment is paramount for healthcare staff - significant numbers have been infected in both Italy and China
^10^. There is a pressing need to identify effective treatments and preventive measures for COVID-19. Testing, isolation and quarantine measures are key in managing the epidemic, but the development of treatments that shorten disease duration, improve outcome, and reduce infectivity is clearly essential, helping both the individual patient and potentially also limiting spread. While novel agents, such as remdesivir, are in development, these will not be available to the vast majority of patients within coming months
^11,
12^. However, repurposing older drugs that are currently licensed and manufactured has the potential to have dramatic impact at both individual and population levels, since roll-out of treatment to the wider population is feasible, affordable and safe. The choice of such drugs to trial should be driven by evidence of
*in vitro* efficacy, plausibility and deliverability of the intervention.

### Scientific rationale

COVID-19 is a respiratory disease caused by a novel coronavirus (SARS-CoV-2) and causes substantial morbidity and mortality. There is currently no vaccine to prevent COVID-19 or therapeutic agent to treat COVID-19. This clinical trial is designed to evaluate potential therapeutics for the treatment of hospitalised people with COVID-19.

We hypothesise that chloroquine slows viral replication in patients with COVID-19, attenuating the infection, and resulting in more rapid decline of viral load in throat/nose swabs. This viral attenuation should be associated with improved patient outcomes. Given the enormous experience of its use in malaria chemoprophylaxis, excellent safety and tolerability profile, and its very low cost, if proved effective then chloroquine would be a readily deployable and affordable treatment for patients with COVID-19.

***Chloroquine***. Chloroquine is an antimalarial drug that was discovered in 1934 and has been widely prescribed for malaria since 1947
^13^. It has been safely prescribed to millions of people in all income settings since then. Chloroquine is inexpensive and simple to administer, is a first-line treatment for non-falciparum malaria, and is on the World Health Organization’s List of Essential Medicines
^14^.

***Antiviral effect***. Chloroquine has recently been reported as a potential broad-spectrum anti-viral drug
^15^. It was found to have significant activity
*in vitro* against the SARS-CoV responsible for the 2003 SARS outbreak in at least 30 countries, where it has been shown to block virus infection by increasing the pH required for viral fusion and by interfering with the glycosylation of cellular receptors of SARS-CoV
^16^. More recently it has been shown to also have significant
*in vitro* activity against SARS-CoV-2, where it functioned both at the cell viral entry and post-entry stages during experimental infection of Vero E6 cells
^15^. A half-maximal effective concentration (EC50 or the concentration associated with a decrease in replication (in Vero E6 cells) of the virus by 50%) of 1.13 µM was reported, with a corresponding EC90 of 6.9 µM
^15^. This effect occurred when the drug was given either before or after viral inoculation
^15^. Activity of chloroquine in the low micromolar range has been confirmed elsewhere
^17^. In addition to its anti-viral effects, chloroquine also has an immunomodulatory effect
*in vivo*, which may synergistically enhance its effect
*in vivo*
^15^.

***Human use in COVID-19***. Chloroquine has a wide volume of distribution and achieves high lung concentrations following oral administration
^18^. The relationship between plasma concentrations and concentrations in respiratory epithelium is not known precisely, though in rats the concentration in the lung is between 124 and 748-fold that in plasma
^19^. The effective concentration needed to inhibit 90% of viral replication (EC90) of 6.9uM is higher than the therapeutic exposures needed to treat malaria, but should be clinically achievable, and maintained, with daily doses of chloroquine ≥500mg/day
^15^.

Chloroquine has been used in patients with COVID-19 in China and South Korea with reported good effect
^20^. However, rigorous, peer-reviewed outcome data are currently lacking and thus it is not possible to draw firm conclusions about its efficacy and safety. A major problem with the non-controlled use of untested treatments in disease emergence is that improvements in outcome that occur naturally over time due to improved general management of cases as clinical experience is accrued, are falsely interpreted as being due to the novel therapy. Despite the lack of data, as of 20th March 2020, chloroquine, in a dose of 500mg twice daily, is recommended for mild, moderate and severe COVID-19 cases in China, and is currently recommended for all patients >70 years old with evidence of pneumonia due to SARS-CoV-19 in Italy
^21^.

***Safety***. Chloroquine has been used extensively as continuous chemoprophylaxis against malaria for individual periods often exceeding five years and has been the prophylactic drug of choice in pregnancy
^22^. It is safe in all age groups. In addition to its antimalarial use, both chloroquine, and the closely related and slightly more hydrophilic hydroxychloroquine, are used in continuous daily dosing for rheumatoid arthritis, systemic and discoid lupus erythematosus and psoriatic arthritis. Chloroquine at a dose of 2.4mg base/kg (155 mg)/day for years is used for rheumatoid arthritis. Chloroquine given at the correct dose has an excellent safety profile.

## Protocol

This protocol has been written according to the SPIRIT guidelines
^23^.
Figure 1 shows the study flowchart.

**Figure 1. f1:**
[figure not shown]
Trial flow chart. ALT, alanine aminotransferase; ULN, upper limit of normal; ARDS, acute respiratory distress syndrome.

The primary aim of this study is to assess the safety and efficacy of chloroquine for the treatment of hospitalized adults with reverse transcription polymerase chain reaction (RT-PCR) confirmed SARS-CoV-2 infection in Vietnam.
****

### Objectives

***Primary objective***. To determine if chloroquine results in more rapid clearance of SARS-CoV-2 from throat/nose swabs of patients with COVID-19.

***Secondary objectives***

To determine if chloroquine shortens the duration of hospital stay.To determine if chloroquine results in more ventilator-free days.To determine if chloroquine use results in better survival compared with standard of care.To define the safety profile of chloroquine in COVID-19.

### Study design

The study will start with a 10-patient prospective observational pilot study following the same entry and exclusion criteria as for the randomized trial and undergoing the same procedures. All 10 participants will receive chloroquine at the doses used in the trial; they will not be randomized. The purpose of the pilot study is to develop the study procedures for the randomized controlled trial, including the safe monitoring of participants, and to acquire some preliminary data on the safety of chloroquine in those with COVID-19 in Vietnam. Data from these patients will not be included in the final analysis. Once the pilot study has been completed, and the data reviewed by the trial steering committee (TSC), the data monitoring committee (DMC), and the Ministry of Health (MoH) ethics committee (EC), we will proceed with the trial. We aim for minimum delay between completing the pilot study and starting the randomized trial.

The main study is an open label, randomised, controlled trial with two parallel arms of standard of care (control arm) versus standard of care with 10 days of chloroquine (intervention arm) with a loading dose over the first 24 hours, followed by 300mg base orally once daily for nine days. The study will recruit patients in three sites in Ho Chi Minh City, Vietnam: the Hospital for Tropical Diseases (HTD), the Cu Chi Field Hospital, and the Can Gio COVID hospital. Additional sites including the National Hospital for Tropical Diseases in Ha Noi, Vietnam will be added based on enrolment rates.

All adult patients (≥18 years old) presenting to the study centres with positive throat/nose swabs (RT-PCR) for SARS-CoV-2 and requiring hospital admission will be eligible for study inclusion subject to the inclusion and exclusion criteria. Randomization will be stratified by severity of illness with severe disease being defined by a SpO2 ≤94%, or tachypnea (respiratory rate ≥24 breaths/min), and mild-moderate disease being defined by SpO2 >94% and respiratory rate <24 breaths/min without supplemental oxygen.

### Endpoints

***Primary endpoint***. The primary endpoint is the time to viral clearance from throat/nose swab. Viral presence will be determined using RT-PCR to detect SARS-CoV-2 RNA. Throat/nose swabs for viral RNA will be taken daily while in hospital until there have at least two consecutive negative results. Virus will be defined as cleared when the patient has had ≥2 consecutive negative PCR tests. The time to viral clearance will be defined as the time following randomization until the midpoint between the last positive and the first of the negative throat/nose swabs.

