***Secondary endpoints***

The duration of hospital stay from the time of randomization.The number of ventilator-free days during the first 28 days following randomization.The time to (all-cause) death following the first 10, 28, and 56 days since randomization.The WHO ordinal outcome scale for COVID-19 at days 28, 42 and 56
^24^.Fever clearance time (defined as temperature <37.5°C for 48 hours).Development of acute respiratory distress syndrome (ARDS) defined by the Kigali criteria
^25^.Oxygenation-free days over the first 28 days.Risk of serious adverse events (SAEs).Risk of grade 3 or 4 adverse events (AEs).

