### Statistics

***Sample size calculation***. We assume the viral clearance time from throat/nose swabs to have a log-normal distribution. Using data from 14 patients in Ho Chi Minh City and Singapore, we estimated the mean time to clearance (natural log scale) of 2.17 days and standard deviation 0.74 ([name] [name], personal communication, 13 February 2020 and [name] [name], personal communication, 12 February 2020). 120 patients will give 80% power to detect a reduction in the time to viral clearance by at least a factor 0.68. If the trial completes enrolment and is not stopped early due to safety, efficacy or futility, we will enrol 240 patients. A sample size of 240 patients will give 80% power to detect a reduction in the time to viral clearance by at least a factor 0.76.

***Statistical and analytical plans***. Study analysis will be according to an
*a priori* defined statistical analysis plan, which will be completed before database locking. The primary endpoint is virological and robust and will be performed by technicians unaware of the treatment allocation of the patient. In that sense the study therefore is blinded. The time to viral clearance will be defined as the time from randomization to the midpoint between the last positive and the first of at least two consecutive daily negative viral PCR tests on throat/nose swab. Data will be illustrated with time to event curves and analysed using the log rank test and Cox model.

***Secondary endpoints***.

Survival until 56 days after randomization

Overall survival will be visualized using Kaplan-Meier curves and modelled using the Cox proportional hazards regression model with stratification by disease severity. In addition, survival will be modelled with a multivariable Cox regression model including the following covariates in addition to the treatment group: age, comorbid conditions (hypertension, cardiac disease, diabetes, ACEA inhibitor or angiotensin receptor blocker use).

AEs

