The frequency of serious and grade 3 and 4 ARs as well as the frequency of specific AEs will be summarized (both in terms of the total number of events as well as the number of participants with at least one event). The proportion of participants with at least one such event (overall and for each specific event separately) will be summarized and (informally) compared between the two treatment groups based on Fisher’s exact test if the expected number in one of the cells is at most one and the chi-square test if expected number in each cell is larger than one.

Analysis of other secondary outcomes

1. The duration of hospital stay from the time of randomization.2. The number of ventilator-free days during the first 28 days following randomization.3. The time to (all-cause) death following the first 10, 28, and 56 days since randomization.4. The WHO ordinal outcome scale for COVID-19 at days 28, 42 and 56
^24^.5. Fever clearance time.6. Development of ARDS defined by the Kigali criteria
^25^.7. Oxygenation-free days over the first 28 days.

The analyses of these secondary endpoints will be defined in the statistical analysis plan.

***Statistical hypotheses***. The primary null hypothesis is that the rate of clearance of virus from throat/nose swabs is not different between chloroquine compared with standard of care therapy.

***Analysis datasets***. The primary analysis population for all analysis is the full analysis population containing all randomized participants except for those mistakenly randomized without COVID-19. Participants will be analysed according to their randomized arm (intention-to-treat). In addition, the primary endpoint will be analysed on the per-protocol population, which will exclude the following participants: major protocol violations and those receiving less than one week of administration of chloroquine for reasons other than death.

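### The trial hypothesises a faster fall in viral load, but no listed endpoint uses quantity of virus; keep clearance as primary and, where the assay gives a quantity, add baseline load and rate of decline

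*Protocol article*

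**What the plan says.** - **Hypothesis** (Abstract; Introduction, Scientific rationale): chloroquine slows replication, "resulting in more rapid decline of viral load in throat/nose swabs".
- **Primary objective** (Objectives): "To determine if chloroquine results in more rapid clearance of SARS-CoV-2 from throat/nose swabs of patients with COVID-19".
- **Use of the assay** (Endpoints, Primary endpoint): "Viral presence will be determined using RT-PCR to detect SARS-CoV-2 RNA". Swabs are frequent: "Throat/nose swabs for viral RNA will be taken daily while in hospital until there have at least two consecutive negative results". Table 3 also schedules one at Visit 1.
- **Endpoint** (same section): "Virus will be defined as cleared when the patient has had ≥2 consecutive negative PCR tests". The event time is the midpoint between the last positive swab and the first negative one.
- **Secondary endpoints** (Endpoints, and again under Statistics): hospital stay, ventilator-free and oxygen-free time, death, the WHO scale, fever clearance, ARDS, SAEs and grade 3-4 adverse events. None is virological.
- **Null hypothesis** (Statistics, Statistical hypotheses): "The primary null hypothesis is that the rate of clearance of virus from throat/nose swabs is not different" between the arms.
- **Primary analysis** (Statistics, Statistical and analytical plans): "Data will be illustrated with time to event curves and analysed using the log rank test and Cox model".

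**The concern.** The stated mechanism is quantitative: the drug should make the viral load fall faster. The endpoint keeps one number per patient, the time at which the swabs turn negative. That time depends on two things: the load at randomisation, which treatment cannot change, and the speed of decline, which treatment is meant to change. Randomisation balances starting load on average, so the comparison of clearance times is fair. It is, however, an indirect test of the hypothesis. Variation in starting load also enters it as noise of unknown size.

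If the trial reports no difference in clearance time, nothing else on the endpoint list shows whether decline itself was unaffected. The endpoint list is set in the protocol. Statistics leaves to the SAP how the listed secondary endpoints are analysed, not which endpoints are listed.

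**Working it through.** **1. The plan's own figure.** Inputs from Sample size calculation: log clearance time has mean 2.17 and SD 0.74; 240 patients, factor 0.76; 120 patients, factor 0.68. Allocation is 1:1. No alpha is given, so two-sided 5% is assumed.

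Power = Φ( |ln f| / (SD·√(2/n per arm)) − 1.96 )

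- 240 patients: 0.2744 / (0.74·√(2/120)) = 0.2744 / 0.0955 = 2.873; Φ(0.913) = 81.9%.
- 120 patients: 0.3857 / (0.74·√(2/60)) = 0.3857 / 0.1351 = 2.855; Φ(0.895) = 81.4%.

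Both agree with the stated 80%. The sizing is on clearance time and is consistent with the endpoint.

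**2. How starting load enters.** Assume a log-linear decline (not in the documents). With A the log10 load above the detection limit at randomisation and k the daily fall, T = A/k and ln T = ln A − ln k. The drug acts on k only. For illustration, take A = 4 log10 (assumed). The median control time is exp(2.17) = 8.76 days, so k = 4/8.76 = 0.457 per day. Under chloroquine k = 0.457/0.76 = 0.601, and T = 4/0.601 = 6.66 days. A treated patient starting at 5 log10 clears at 5/0.601 = 8.32 days, close to the untreated patient who starts at 4.

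**3. Analytic value of adjusting for A.** Let p be the share of the variance of ln T due to starting load. Perfect adjustment leaves SD 0.74·√(1−p). The step 1 formula at 240 patients then gives:

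- p = 0: 81.9%
- p = 0.10: SD 0.702, 85.7%
- p = 0.25: SD 0.641, 91.3%
- p = 0.50: SD 0.523, 98.2%

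The documents do not give p.

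**4. Simulation.** Assumptions: A and k log-normal, k multiplied by 1/0.76 under chloroquine, 4 log10 above the detection limit at baseline, daily noisy swabs, the plan's midpoint rule, 120 per arm, and control log-time SD calibrated to about 0.74. Power (%) is shown as planned Cox / Cox with baseline load / comparison of per-patient slopes. The first column has 1000 replicates; the others have 500 (error about 2 points).

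| p | swab noise SD 0.3-0.7 log10 | 0.5 | 1.0 | 1.5 |
|---|---|---|---|---|
| 0 | 69-71 / 69-70 / 78-79 | 67 / 67 / 78 | 68 / 69 / 76 | 67 / 69 / 67 |
| 0.10 | 70 / 72-74 / 82-85 | not run | not run | not run |
| 0.25 | 71-72 / 79-81 / 87-88 | 71 / 82 / 87 | 66 / 75 / 79 | 64 / 70 / 67 |
| 0.50 | 71-72 / 89-94 / 95-98 | 72 / 92 / 95 | 64 / 87 / 85 | 65 / 81 / 77 |

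The Cox-against-Cox comparison isolates the covariate. A further set of runs put its gain at about 0 points (p = 0), +2 to +5 (0.10), +6 to +11 (0.25) and +18 to +23 (0.50). The table agrees within simulation error; its noisiest cell at p = 0.50 gives 81 − 65 = +16.

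**5. Slopes are not reliably better.** The slope advantage in the table partly reflects the inefficiency of Cox for log-normal times, which is a separate matter. Against a t-test on log clearance time (300 runs, error about 2.5 points), slopes gave:

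- noise 1.0: 75 v 80% (p = 0), 79 v 80% (0.10), 76 v 77% (0.25)
- noise 1.5: 68 v 75%, 68 v 72%, 68 v 69%

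A second model, with normally distributed starting load and weighted slopes, compared slopes with the log-rank test. The change ran from about +11 points at noise 0.5 (75% to 86%) to about −14 at noise 1.5 (79% to 66%).

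**The case against.** **The plan is internally consistent.** Objective, endpoint, null hypothesis and sample size all concern clearance. A reader might infer that the primary endpoint contradicts the hypothesis. It does not: if the drug speeds decline and starting load is balanced, clearance comes sooner. The cut at negativity also has a clinical use, since Subsequent assessments ties discharge to two consecutive daily negative swabs. This stands, and is why clearance should remain primary.

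**The assay may not be quantitative.** A reader might infer that the plan throws away viral loads it already holds. The article speaks only of detecting RNA and mentions no Ct value, copy number or detection limit. This also stands, so the recommendation is conditional.

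**Loss of power is not shown.** A reader might infer that the plan loses power by using a positive/negative result. The trial meets its stated 80% for the endpoint it chose. Whether slopes would do better depends on swab noise and baseline spread that the documents do not give, and the simulated model places the effect on the slope from day 0, which favours slopes. The left-censored mixed model proposed below was not itself simulated. A secondary endpoint adds no power to the primary test in any case.

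**Covariates belong to the SAP.** This is fair: the absence of a baseline-load covariate from the article is not itself a fault. It is recommended because it is the part of the change that can help the primary test, and it requires the quantity to be recorded.

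**Urgency.** The Discussion links early stopping to the pace of other chloroquine trials, so slow recruitment should not be read into it.

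What none of this answers is that the stated mechanism has no endpoint of its own.

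**Conclusion.** The point holds as a gap in alignment that is cheap to close, not as an error in the primary analysis. The hypothesis concerns decline of viral load, and no listed endpoint measures it. A null result on clearance time would leave that hypothesis only indirectly tested.

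The possible gain in primary power comes from the baseline covariate alone: about 0 points if starting load explains none of the variance in log clearance time, about 2-5 at 10%, 6-11 at 25% and 18-23 at 50%. These figures rest on log-linear decline, 4 log10 above the detection limit at baseline, two-sided 5%, and the plan's mean, SD, factor and sample size. The covariate cost no power beyond simulation error in any setting run. The case for the slope endpoint is that it tests the stated mechanism directly; its power relative to clearance time can go either way.

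**What to change.** Keep time to viral clearance as the primary endpoint. Where the RT-PCR yields a Ct value or copy number, record it for every swab already scheduled. Then:

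1. Include log viral load (or Ct) from the Visit 1 swab as a prespecified covariate in the primary Cox model.
2. Add rate of decline of log viral load as a prespecified secondary endpoint, compared between arms by a linear mixed model with random intercept and slope and an arm-by-time interaction, treating values below the detection limit as left-censored.

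The cost is one numeric field per swab and a few lines in the endpoint list and analysis text, with no extra swabs, visits or patients. The real burden is comparability: with three sites and more possible, Ct values need a common assay, a calibration between laboratories or a site term. If the assay gives no usable quantity, neither addition can be made; the protocol should then say that decline of viral load is inferred from clearance only.
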